### Analysis Methods

The effect of sTM, Syndecan-1 and PECAM-1 on the primary outcome is analysed using cox regression and reported as cause-specific hazards using the method of Ozenne et al.^21^ A separate model is fitted for each of the explanatory variables of interest and each model is controlled for the abovementioned variables.

The effect of the markers of endothelial damage on the risk of death from any cause at 30 days is modelled with cox regression and controlled for the same variables as the analysis of the primary outcome.

We model the effects of continuous variables with restricted cubic splines with 2 knots^22^ if the introduction of splines significantly improves model fit as evaluated by the Wald Statistic.

The effect of the markers of endothelial damage on the PAF-ratio on the first day of ICU-admission and on last PAF-ratio in patients dying within 5 days of inclusion is modelled with linear regression and controlled for COPD, age, respiratory infection and shock (defined as need for vasopressor and a lactate >= 2).

All models will be examined for standard measures of model fit and assumptions and the included variables will be transformed as appropriately. We test for biological plausible interactions such as between levels of the biomarkers of endothelial damage and septic shock or respiratory infection. Interaction terms will be kept in the model if they are significant in the multivariable analysis based on the p-value for the effect of the interaction term.

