### Sample size

As previous data on the levels of sTM, Syndecan-1 and PECAM-1 in a critically ill population of patients with acute respiratory failure are very scarce, formal power calculations were not possible to perform and the results should be considered exploratory.

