# Statistical Principles

A p-value below 0.05 is considered significant. 95% Confidence Intervals (95% CI) are presented along with point estimates where feasible.

Results from both the univariable and multivariable analysis are presented where relevant.

No correction for multiple comparisons is performed, as all study results will be regarded as exploratory.

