### Variables

The explanatory variables of interest are sTM, Syndecan-1 and PECAM-1. These are continuous and presented in ng/ml. They will also be introduced to the regression models as categorical variables divided into three groups: =< 25^th^ percentile, > 25^th^ and =< 75^th^ percentile, > 75^th^ percentile

To be controlled for in the multivariable analyses are the following known predictors of poor outcomes in the ICU: Gender, Age, A history of Chronic Inflammatory Pulmonary Disease (COPD), Septic Shock at ICU-admission, A history of Heart Failure, Worst PAF-ratio on the first day of ICU-admission, The presence of Respiratory Infection at ICU-admission, Acute Kidney Injury during the first day of ICU-admission and highest Bilirubin during first day of ICU-admission.

Septic shock is defined in accordance with the “Third international consensus definition for sepsis” as suspected or confirmed infection plus the need of vasoactive medication to maintain a mean arterial blood pressure of 65 and a blood lactate of 2 or more.^18^

COPD, Heart Failure and Acute Respiratory Infection are adjudicated by one author ([name]) based on information from the EMR without knowledge of the results of the primary outcome or of the values of sTM, Syndecan-1 or PECAM-1.

PAF-ratio is calculated with information from the EMR as the values of PaO2 and FiO2 giving the lowest ratio on a given day of ICU-admission.

Acute Kidney Injury is defined as stage 2 or more from the KDIGO guidelines and calculated based on the worst creatinine during the first day of ICU-admission.^19^ Baseline creatinine is defined as the median of all creatinine levels from 180 to 8 days prior to ICU-admission. In patients without a baseline creatinine, the creatinine levels is estimated with revised Lund-Malmö formula assuming a normal GFR of 70 ml/min/1,73m2.^20^

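### Read literally, a restricted cubic spline with 2 knots is a straight line, so the planned Wald check for non-linearity has no terms to test

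*SAP*

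**What the plan says.** The SAP's Analysis Methods section sets one rule for the shape of continuous effects: "We model the effects of continuous variables with restricted cubic splines with 2 knots", applied "if the introduction of splines significantly improves model fit as evaluated by the Wald Statistic". Statistical Principles gives the threshold: "A p-value below 0.05 is considered significant". The SAP gives no knot positions, degrees of freedom or software function, and it does not distinguish interior from boundary knots. The software section names only R 3.6.1.

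The rule covers the three markers, of which the Variables section says "These are continuous and presented in ng/ml". It also covers the continuous adjustment variables: age, worst PAF-ratio and highest bilirubin.

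Two other provisions bear on shape. For the markers, Variables adds: "They will also be introduced to the regression models as categorical variables divided into three groups", cut at the 25th and 75th percentiles. Analysis Methods also says that "the included variables will be transformed as appropriately".

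**The concern.** A restricted cubic spline is constrained to be linear beyond its outermost knots. With only two knots, those constraints remove all the curvature between them as well. The planned spline is then the linear term under another name, and the test meant to decide between the two has nothing to test.

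The spline is the only method the SAP names for the shape of a continuous effect, and the three markers are the exposures of interest in every model. If the step cannot be run, an analyst must either fit straight lines throughout or improvise a different spline after seeing the data. Two analysts following the same sentence could fit a 1-df line and a 3-df curve.

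**Working it through.** **Inputs.** From Analysis Methods: restricted cubic spline, 2 knots, Wald test against the linear fit. From Statistical Principles: significance at 0.05. The SAP gives no sample size, event count or power figure, so there is no stated number to reproduce. The check is algebra and does not depend on sample size.

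**Counting terms.** A cubic spline with k knots t₁ < … < t_k has 4 + k coefficients: b₀, b₁, b₂, b₃ for the cubic, and g₁, …, g_k for the truncated cubes.

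- Linear below the first knot: b₂ = 0 and b₃ = 0.
- Linear above the last knot: Σg_j = 0 and Σg_j t_j = 0.

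These are 4 independent constraints, so (4 + k) − 4 = k free parameters remain, including the intercept. That leaves k − 1 slope terms, of which k − 2 are non-linear.

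**Putting in k = 2.** The upper-tail constraints become g₁ + g₂ = 0 and g₁t₁ + g₂t₂ = 0. Substituting g₂ = −g₁ gives g₁(t₁ − t₂) = 0. As t₁ ≠ t₂, both g₁ and g₂ are zero and only b₀ + b₁x is left.

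| Knots in total | Slope terms | Non-linear terms | df of Wald test for non-linearity |
|---|---|---|---|
| 2 | 1 | 0 | 0 (undefined) |
| 3 | 2 | 1 | 1 |
| 4 (also 2 interior + 2 boundary) | 3 | 2 | 2 |

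**Numerical confirmation.** The basis was built on 500 simulated log-normal values. With 2 knots it had one column, whether the knots stood at the 10th and 90th percentiles or at the tertiles. For a simulated curved relation, the residual sums of squares were:

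- straight line: 102.954
- 2 knots: 102.954
- 3 knots: 85.54
- 4 knots: 70.75

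The 2-knot fit is identical to the line.

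**What the other planned analysis recovers.** This is a simulation under assumptions that the SAP does not supply: n = 200, log-normal marker, liberation hazard 0.12/day, death hazard 0.03/day, 300 fits per scenario. The sizes of the last three effects are also assumed. Power was:

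| True shape | Linear in ng/ml | Three percentile groups | 4-knot spline of log marker |
|---|---|---|---|
| Log-linear, HR 0.78 per SD of log | 62% | 68% | 73% |
| Plateau | 49% | 97% | 95% |
| U-shape | 31% | 57% | 76% |
| Top-quartile threshold | 27% | 39% | 28% |

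In the log-linear case a plain log term reached 87%, so the spline's gain over the ng/ml line there reflects the log scale rather than the knots. The figures are illustrative only.

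**Choosing the form by the test.** This matters only once the spline works. With no true effect and the same n and hazards (600 runs, 4 knots in ng/ml), using the spline if non-linearity p < 0.05 and the line otherwise rejected 8.3% of the time at a nominal 5%. The Monte Carlo standard error is √(0.083 × 0.917 / 600) ≈ 1.1 points. A spline of the log marker kept in every run rejected 4.2%. Because the two procedures also differ in scale, the gap between them is not due to selection alone.

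**The case against.** The strongest reply is that the count of knots is a convention. In natural-spline parameterisations only interior knots may be counted, with boundary knots added. Two knots then mean four in total, and the 2-df test is valid. That reading is possible, and the guide cited for the splines is not at hand to settle it. But nothing in the SAP states it, and a restricted cubic spline is usually described by all its knots. Under the literal reading the step cannot be run. Under the other it is under-specified. The sentence needs changing in both cases.

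The second reply concerns consequences, and most of it stands. A reader might infer that the plan is locked to a straight line in ng/ml, so that a plateau or U-shape would be missed and the primary question wrongly answered as no association. The SAP does not support that. The three-group analysis of the markers is planned unconditionally and can show such shapes. In the simulation above it matched the spline for the plateau, beat it for the threshold, and fell clearly behind only for the U-shape. Transformation, including to a log scale, is permitted. The Sample size section adds that "formal power calculations were not possible to perform and the results should be considered exploratory".

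These provisions soften the effect without repairing the rule. The groups cover only the markers, not age, PAF-ratio or bilirubin, and the transformation clause gives no criterion.

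A last reply is that the plan cannot be faulted at once for a test that never selects and for selecting by a test. That is fair: the post-selection point applies only to a workable spline, and so bears on how the repair is written.

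**Conclusion.** The rule is wrong as written. Counting all knots, it specifies a spline with 0 non-linear coefficients and a Wald test with 0 df, so it cannot detect non-linearity in any continuous variable. This conclusion is exact and rests only on that counting convention. If interior knots were meant, the defect is an omission: the model is then a 3-slope-term curve with a 2-df test, and the SAP must say so.

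The importance is moderate. For the markers, the percentile groups and permitted transformations leave other routes to a non-linear effect. For age, PAF-ratio and bilirubin there is only the open-ended transformation clause, so adjustment may be linear where it should not be. The size of any resulting distortion cannot be derived from the SAP, which gives no sample size, event count or marker distribution.

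**What to change.** Replace the spline sentence. Possible wording: *Continuous variables are modelled with restricted cubic splines with 3 knots in total, at the 10th, 50th and 90th percentiles. Non-linearity is assessed by the joint Wald test of the k − 2 non-linear terms (1 df).*

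Four knots at the 5th, 35th, 65th and 95th percentiles (2-df test) would serve equally well. The choice should be fixed before the data are analysed. If two interior plus two boundary knots were intended, state that, with the positions and the 2-df test.

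For the markers, preferably report the overall Wald test of all spline terms whatever the non-linearity p-value, because choosing the form by that test makes the reported p-value and confidence interval post-selection. A log scale for the markers is a reasonable option, but this error does not require it.

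The cost is one sentence, plus 1 extra df per splined variable with 3 knots or 2 with 4 knots. Each Cox model has a marker and nine adjustment variables, of which four in all are continuous (marker, age, PAF-ratio, bilirubin). Splining all four adds 4 × 1 = 4 or 4 × 2 = 8 df. As no event count is stated, that is a reason to consider the smaller spline, or to limit which covariates are splined, and to say so in advance.

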# Introduction

### Background and Rationale

Acute respiratory failure is a common reason for admission to the Intensive Care Unit (ICU), and it is estimated that 13-20 million patients are mechanically ventilated worldwide annually^1^ with more than a third dying during the hospital admission, although studies suggest that the mortality have improved in recent years.^2–45^

Endothelial dysfunction has been proposed as a plausible link between critical illness and multiorgan failure^6^ and two Danish Randomized Controlled Trials (RCT) are currently testing the prostacyclin analogue Ilomedin as a targeted treatment against endotheliopathy in trauma and septic shock.

In experimental models, pathologic stimuli to the pulmonary endothelium results in the inflammation and noncardiogenic pulmonary oedema that are hallmarks of ARDS.^7–9^

In ARDS increased permeability of the intercellular connections between endothelial cells leads to fluid accumulating in the alveoli. A yet unpublished study found that Platelet Endothelial Cell Adhesion Molecule (PECAM-1) is the best marker for this interruption of the cell-cell junctions between the endothelial cells.

In clinical studies, soluble thrombomodulin (sTM) and Syndecan-1 are valid markers of damage to the profound endothelium and endothelial glycocalyx, respectively.^10^ In critically ill patients, both markers increase with more severe disease and predicts liver and renal failure.^10,11^ Increased sTM levels are associated to fewer ventilator free days,^12^ organ failure^13,14^ and mortality^14^ in patients with ARDS.

Syndecan-1 associates with acute respiratory failure in patients with pulmonary sepsis^15^ and severe sepsis after resuscitation with large volumes of fluids.^16^ Nevertheless, surprisingly both markers correlates poorly with hypoxaemia at ICU admission and need for mechanical ventilation.^10^

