# Trial Population

### Screening data

The ICU at Copenhagen University Hospital – North Zealand, Copenhagen, Denmark is a 12 bed, mixed surgical/medical ICU with around 900 admissions per year.

Between November 2016 and June 2019 all patients presenting to the ICU were screened for inclusion in the Metabolomics Study.

Unfortunately, no screening log was kept at the time.

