### Eligibility

The inclusion criteria consisted of age > 18, acutely admitted to the ICU and a presumed stay > 24 h. The exclusion criteria were non-obtainable informed consent or active treatment deemed futile by the treating clinician.

Included patients had study blood samples drawn daily for the first 5 days of their ICU-stay or until death or discharge, whichever came first.

For the present study in the Metabolomics cohort, only patients that presented with acute respiratory failure are included. Acute respiratory failure is defined as patients receiving either Invasive (IV) or Non-Invasive Ventilation (NIV) on the first day of ICU-admission.

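### The liberation and 30-day death models adjust for septic shock only, while the PAF-ratio models adjust for shock of any cause; non-septic shock is left in the reference group as residual confounding.

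*SAP*

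**What the plan says.** The covariate list under Variables contains one shock term: "Septic Shock at ICU-admission, A history of Heart Failure, Worst PAF-ratio on the first day of ICU-admission". The same section gives this definition of septic shock: "suspected or confirmed infection plus the need of vasoactive medication to maintain a mean arterial blood pressure of 65 and a blood lactate of 2" (the lactate value is a minimum). The rest of the list is gender, age, COPD, respiratory infection, acute kidney injury (AKI) and bilirubin.

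Analysis Methods applies this list to the primary outcome ("each model is controlled for the abovementioned variables"). It applies the same list to 30-day death ("modelled with cox regression and controlled for the same variables as the analysis of the primary outcome").

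The two PAF-ratio outcomes get a different list in the same section: "controlled for COPD, age, respiratory infection and shock (defined as need for vasopressor and a lactate >= 2". This shock term has no infection criterion and no stated time window. History of heart failure is absent from this list.

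Infection is not an entry condition. Under Eligibility, "Acute respiratory failure is defined as patients receiving either Invasive (IV) or Non-Invasive Ventilation (NIV) on the first day of ICU-admission", and Screening data describes a "mixed surgical/medical ICU with around 900 admissions per year".

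**The concern.** A patient on a vasopressor with a raised lactate but no infection counts as shocked in the PAF-ratio models and as having no septic shock in the primary and mortality models. In the Cox models that patient sits in the same reference group as patients without shock.

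The SAP's own rationale makes such patients plausible confounders. Of sTM and Syndecan-1, Background and Rationale says that "both markers increase with more severe disease and predicts liver and renal failure", and it names trauma as well as septic shock as a setting for endothelial treatment. If non-septic shock raises the markers, slows liberation and increases deaths, part of its effect is credited to the marker. That error runs in the direction of the study hypothesis, and it falls on the primary outcome. Under Objectives, the results are meant to inform prognostication and later treatment trials.

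A smaller matter concerns the day-1 PAF-ratio model. The background is about noncardiogenic oedema, yet the adjudicated heart-failure history is not used where cardiac oedema would lower the outcome directly.

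**Working it through.** **Comparison of the text.**

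| Model | Shock covariate | Infection required | Timing | Heart failure history |
|---|---|---|---|---|
| Liberation (primary) | septic shock | yes | ICU admission | included |
| 30-day death | septic shock | yes | ICU admission | included |
| PAF-ratio, day 1 and last | vasopressor and lactate >= 2 | no | not stated | not included |

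The two shock definitions differ essentially in the infection requirement. The data that separate septic from other shock are therefore already needed for the planned models.

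**Size.** The SAP has no figure to reproduce: it states no sample size, event count or shock prevalence. Every input below is an assumption.

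Let pS be the share with septic shock, pN the share with other shock, d the marker shift in shock (in SDs within shock group), and HR the hazard ratio of shock. The marker has no effect of its own (true HR 1).

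- Share with other shock among patients without septic shock: q = pN / (1 − pS).
- Set A = (1 − pS) × q × (1 − q). Given septic shock, the slope of the other-shock indicator on the marker is b = A·d / (1 + A·d²).
- The apparent marker HR per SD is then about HR^b.

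Example with pS = 20%, pN = 20%, d = 1.0:

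- q = 0.20/0.80 = 0.25.
- A = 0.80 × 0.25 × 0.75 = 0.150.
- b = 0.150/1.150 = 0.130.
- Liberation: 0.6^0.130 = 0.936. Death: 2^0.130 = 1.095.

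The formula is compared below with simulated Cox models for liberation (two cohorts of 8,000 per scenario, pS = 20%, AKI and heart failure also in the model). The simulated shift is the septic-only marker HR divided by the any-shock marker HR.

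| pN | d | HR of shock | b | Formula | Simulation |
|---|---|---|---|---|---|
| 5% | 0.3 | 0.8 | 0.014 | 0.997 | 1.002/1.005 = 0.997 |
| 5% | 1.0 | 0.6 | 0.045 | 0.977 | 0.995/1.016 = 0.979 |
| 10% | 0.6 | 0.6 | 0.051 | 0.974 | 0.974/0.999 = 0.975 |
| 20% | 0.6 | 0.6 | 0.085 | 0.957 | 0.966/1.005 = 0.961 |
| 20% | 1.0 | 0.6 | 0.130 | 0.936 | 0.946/1.009 = 0.938 |

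Simulation noise is about 0.01 to 0.02, so the two agree. The liberation shift is about 0 to 6%, and at most about 2% when non-septic shock is 5%.

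For death, a separate simulation (pS = 15%, pN = 10% to 20%, d = 0.5 to 0.8, HR 2.0, no other covariates) gave 1.03 to 1.09 per SD. The formula gives 1.030 and 1.080 at the same two ends.

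**Do the planned covariates absorb it?** This depends on how shock acts.

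- AKI added, pN = 10% to 20%, d = 0.5 to 0.8: 0.980 to 0.940 for liberation and 1.035 to 1.087 for death. A three-level shock term returned 0.997 to 1.001 and 0.990 to 1.004.
- AKI, bilirubin and PAF-ratio added, with part of the shock effect running through organ dysfunction: the worst case (pN = 20%, d = 0.8) shrinks from 0.940 to 0.971 for liberation and from 1.072 to 1.036 for death.
- The same three terms added, with the whole shock effect direct: the worst case stays at 0.957 and 1.082.

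**The case against.** **All inputs are assumed.** No section shows that shock without infection is common in this ventilated subgroup; a mixed unit only makes it possible. This stands, and it is why only a range is given.

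**Other covariates stand in for shock.** The Cox models also contain AKI, bilirubin, PAF-ratio and heart failure. This stands in part: they can roughly halve the shift, or hardly change it. A reader might infer that the primary model is otherwise unadjusted for severity. The list under Variables shows that it is not.

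**Shock may lie downstream of endothelial damage, so adjusting could remove part of the effect of interest.** This does not carry the point. The plan already adjusts for septic shock, AKI and bilirubin, which raise the same question, and it treats any-cause shock as a covariate elsewhere.

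**Two lists are not in themselves an error.** This is right. The PAF-ratio cannot be adjusted for itself, and a shorter list is defensible for the last PAF-ratio, which covers only patients who die within 5 days. What lacks a reason is the narrower shock definition in the main models.

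**The study is declared exploratory.** That excuses the absence of power and multiplicity control and lowers the stakes. It does not justify confounding that available data could reduce.

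**Heart failure.** A reader might infer that low PAF-ratios from cardiac oedema will be taken for endothelial damage, and that this covariate prevents it. Neither follows from the SAP: the covariate is a history, not acute cardiac oedema, so it helps only in part, and the size of this effect was not estimated.

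**Conclusion.** The point holds as one of residual confounding, small to modest in size. The differing shock terms are plain in the text and unexplained. For a marker with no effect, the assumed ranges give a shift of about 0 to 6% per SD for liberation and up to about 9% for death, less if the other day-1 covariates absorb part of it. The direction, towards slower liberation and more deaths at higher marker levels, rests on the assumption that non-septic shock raises the markers and worsens outcome. The SAP's background makes this likely but does not establish it for this cohort.

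A reader might go further and infer that non-septic shock could explain any marker association found, or that the primary analysis is invalid. The documents do not support that: they give no prevalence, and even the extreme corner of the assumed range moves the HR by less than a tenth per SD. The change is still worth making, because it is cheap and concerns the primary outcome.

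**What to change.** 1. Under Variables, replace the septic-shock covariate by a three-level variable: no shock; septic shock as now defined; other shock, meaning vasopressor need and lactate >= 2 without suspected or confirmed infection. Assess all levels over one stated window, ICU admission or day 1, and give the shock term of the PAF-ratio models a stated window too.
2. Use this variable in the liberation and 30-day death models. Keep the septic level for the planned marker interaction.
3. State in advance that the variable collapses to any-cause shock if the other-shock level is too sparse. The SAP gives no sample size from which to judge this now.
4. Minor: add history of heart failure to the day-1 PAF-ratio model, and note that it captures acute cardiac oedema only partly.

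If the sponsor prefers the narrower term, the SAP should justify it and add the three-level model as a sensitivity analysis.

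The cost is SAP wording and one extra parameter per model, with an imprecise estimate for the other-shock level if few patients fall in it. No new data are needed, since the planned shock definitions already use vasopressor need, lactate and infection, and heart failure history is adjudicated.

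### Keeping marker interactions only when significant lets a test decide whether the reported marker effect is a cohort effect or a reference-group effect

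*SAP*

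**What the plan says.** The SAP's Objectives section sets out to estimate how each marker affects time to liberation in a broad ICU cohort with acute respiratory failure.

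Under Variables: "The explanatory variables of interest are sTM, Syndecan-1 and PECAM-1". On coding it says "These are continuous and presented in ng/ml" and then "They will also be introduced to the regression models as categorical variables divided into three groups", cut at the 25th and 75th percentiles. Neither coding is named primary.

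Under Analysis Methods, "A separate model is fitted for each of the explanatory variables of interest and each model is controlled for the abovementioned variables". On interactions: "We test for biological plausible interactions such as between levels of the biomarkers of endothelial damage and septic shock or respiratory infection". The rule that follows is "Interaction terms will be kept in the model if they are significant in the multivariable analysis based on the p-value". The section does not say which marker effect is reported once a term has been kept.

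Statistical Principles supplies the threshold, "A p-value below 0.05 is considered significant", and the stance on multiplicity: "No correction for multiple comparisons is performed, as all study results will be regarded as exploratory".

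**The concern.** The interaction rule does more than add a secondary test: its result changes the model from which the marker effect is read. A marker whose interactions all miss the threshold gets a cohort-level hazard ratio. A marker with one retained term gets a coefficient that applies only to patients without the modifier. With both named terms retained, it applies only to patients with neither. The same marker may fall on different sides of this line in its two codings, or for liberation and for 30-day death.

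Two things are at stake. First, the quantity reported for a given marker may not be the one in the Objectives, and the reader cannot know in advance which it will be. Second, an interaction shown only because it was significant is biased away from the null, and its interval is computed as if the model had been fixed beforehand. The Objectives section hopes the results will support prognostication and prepare the way for targeted trials. An exaggerated contrast between patients with and without septic shock could mislead that use.

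**Working it through.** **Inputs.** From the SAP: a 5% threshold (Statistical Principles; two-sided Wald tests assumed, since sidedness is not stated), three markers (Variables) with one model each, and two named candidate interactions per marker (Analysis Methods). Two is a floor because the list is open. The SAP gives no sample size, event count or prevalence of septic shock, so it has no derived figure to reproduce. Those quantities are assumed below.

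**Step 1: what the coefficient means.** Let M be the marker and S septic shock (0/1). Without interaction, the log hazard contains βM, and exp(β) applies to the cohort. With interaction it contains βM + γS + δMS. The marker hazard ratio is then exp(β) when S = 0 and exp(β + δ) when S = 1, so the coefficient β refers to patients without shock.

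**Step 2: how often the switch happens when no interaction exists.** For one outcome and one coding, with independent tests:

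- one marker, two tests: 1 − 0.95² = 0.0975, about 10%;
- three markers, six tests: 1 − 0.95⁶ = 0.265, about 27%.

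If the rule is applied to all four outcomes, there are 3 × 4 × 2 = 24 tests in one coding. On average 24 × 0.05 = 1.2 terms would then be kept by chance, whatever the correlation between tests.

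A null simulation of one marker's Cox model gave somewhat higher rates than 9.75% in most settings. It assumed 30% septic shock, 40% respiratory infection, a normally distributed marker, competing death and censoring at day 30, with 1,500 data sets per sample size.

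| Assumed n | Kept ≥1, continuous | Kept ≥1, three groups | Codings disagree on keeping |
|---|---|---|---|
| 100 | 12.2% | 13.7% | 15.2% |
| 200 | 12.1% | 12.8% | 13.0% |
| 400 | 11.5% | 9.5% | 12.4% |

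**Step 3: what happens when an interaction does exist.** Assume a true hazard ratio per SD of 0.9 without shock and 0.7 with shock, 30% shock, n = 300, and 1,000 data sets.

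- A prevalence-weighted average gives exp(0.7 × ln 0.9 + 0.3 × ln 0.7) = exp(−0.181) = 0.83. The simulated model without interaction gave 0.84.
- The marker coefficient in the model with the shock interaction averaged 0.90, the no-shock value.
- The term was kept in 39% of runs. In those runs the hazard ratios averaged 0.93 without shock and 0.61 with shock.
- On the log scale the true contrast is ln(0.7/0.9) = −0.25. In the retained runs it was ln(0.614/0.932) = −0.42. A linear-model approximation at an assumed n of 200 gave a similar shift, from −0.25 to −0.41.

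So the same truth is summarised as about 0.84 in 61% of runs. In the other 39% it is summarised by a marker coefficient of about 0.93 with an inflated contrast.

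**Step 4: confidence intervals.** A single-coefficient term is kept by a 5% Wald test exactly when its 95% Wald interval excludes zero. If the true interaction is zero, none of the retained intervals contains the truth.

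**The case against.** The strongest reply is that the plan is openly exploratory. Sample size and Statistical Principles both say so, multiplicity is deliberately uncorrected, and no family-wise rate is claimed. That stands. A reader might infer that the 5% threshold misstates an error rate the plan promised to control, but the document promises none. The 10% and 27% are given here only to show how often the form of the model would change by chance.

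A second reply is that the SAP never says the lone marker coefficient will be reported. Stratum-specific hazard ratios from a retained interaction would be ordinary and interpretable. This is fair, and it limits the harm if that is the intention. It does not remove the selection: strata would be shown only where the test was significant, which is where the contrast is exaggerated.

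A reader might also infer that the data choose the coding. The text does not support this. Both codings are fitted, the percentile cut-points are fixed in advance, and no rule picks between them. What is missing is a label saying which coding is read first.

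Finally, a reader might infer that a planned comparison between the markers is spoilt. No such comparison is planned, and coefficients per ng/ml of different molecules would not be directly comparable anyway.

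**Conclusion.** The point holds for the interaction rule. As written, a significance test decides whether each marker's reported effect is the cohort-level effect in the Objectives or an effect at the modifier's reference level. Retained contrasts are overstated, with intervals that ignore the selection.

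Under the null, about 10% of marker models would keep at least one of the two named interactions, and about 27% of studies would keep at least one over three markers. These figures assume independent tests at 5%, one outcome and one coding. The exaggeration from −0.25 to about −0.4 on the log scale rests on assumed effects, sample size and, for the Cox result, shock prevalence.

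The exploratory label settles the multiplicity question but not what the reported effect means. The absence of a named primary coding is a minor gap beside this. The plan should be changed, and the change is small.

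**What to change.** Replace the retention rule in Analysis Methods with wording to this effect:

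> For each marker and each outcome, the primary model contains the marker and the listed covariates and no interaction terms. Effect modification is examined for septic shock and respiratory infection only, each in a separate secondary model. Marker estimates with 95% CIs are reported in each stratum, with the interaction p-value, whatever that p-value is.

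The two PAF-ratio models adjust for a shock variable that is not restricted to infection, so the text should state which shock variable is the modifier there.

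As a minor addition under Variables, name the continuous coding as primary and the three-group coding as supportive, with one overall 2-df test if it is tested. No particular transformation or compulsory spline is needed for this point.

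The cost is SAP wording only: no new data, and neither of the two named interaction analyses is lost. One small downside is that, if a true interaction exists, the primary estimate is an average over strata. The stratum estimates reported beside it show this.
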